## 949 16.2 Assessments of Adverse Events

950 Each adverse event will be assessed for severity, causality, seriousness and expectedness  
951 as described below.

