## 16 RECORDING AND REPORTING OF EVENTS AND INCIDENTS

### 16.1 Definitions of Adverse Events

| Term               | Definition                                                                                                  |
|--------------------|-------------------------------------------------------------------------------------------------------------|
| Adverse Event (AE) | Any untoward medical occurrence in a patient or study participant, which does not necessarily have a causal |

Cognitive Impairment in Long Covid: Phenotyping and Rehabilitation (CICERO) EDGE 143067; IRAS 302920; Protocol v1.13; 20/12/2024 30/39

|                                                                                                                                                                                                                                                                                                                                                                                                                                           |                                                                                                                                                                                                                                                                                                                                                                                                     |
|-------------------------------------------------------------------------------------------------------------------------------------------------------------------------------------------------------------------------------------------------------------------------------------------------------------------------------------------------------------------------------------------------------------------------------------------|-----------------------------------------------------------------------------------------------------------------------------------------------------------------------------------------------------------------------------------------------------------------------------------------------------------------------------------------------------------------------------------------------------|

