|                                                                                                                                                                                                                                                                                                                                                                                                                                           | relationship with the procedure involved.                                                                                                                                                                                                                                                                                                                                                           |
| Serious Adverse Event (SAE).                                                                                                                                                                                                                                                                                                                                                                                                              | Any adverse event that: 
 
• results in death,
 
• is life-threatening*,
 
• requires hospitalisation or prolongation of existing hospitalisation**,
 
• results in persistent or significant disability or incapacity,
 
 or 
 
• consists of a congenital anomaly or birth defect
 
 |
| 
*A life- threatening event, this refers to an event in which the participant was at risk of death at the time of the event; it does not refer to an event which hypothetically might have caused death if it were more severe.
 
** Hospitalisation is defined as an in-patient admission, regardless of length of stay. Hospitalisation for pre-existing conditions, including elective procedures do not constitute an SAE.
 |                                                                                                                                                                                                                                                                                                                                                                                                     |

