### 952 16.2.1 Severity

953 The generic categories below are given for use as a guide.

| Category | Definition                                                                                                                                                               |
|----------|--------------------------------------------------------------------------------------------------------------------------------------------------------------------------|
| Mild     | The adverse event does not interfere with the participant's daily routine, and does not require further procedure; it causes slight discomfort                           |
| Moderate | The adverse event interferes with some aspects of the participant's routine, or requires further procedure, but is not damaging to health; it causes moderate discomfort |
| Severe   | The adverse event results in alteration, discomfort or disability which is clearly damaging to health                                                                    |

954

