### 967 16.2.3 Expectedness

| Category          | Definition                                                                                                                  |
|-------------------|-----------------------------------------------------------------------------------------------------------------------------|
| Expected   | An adverse event which is consistent with the information about the procedure clearly defined in this protocol .     |
| Unexpected | An adverse event which is not consistent with the information about the procedure clearly defined in this protocol . |

968 \* this includes listed events that are more frequently reported or more severe than previously  
969 reported

970 **16.3 Recording adverse events**

971

972 All adverse events will be recorded in the CRF with clinical symptoms and accompanied with

973 a simple, brief description of the event, including dates as appropriate.

975

976 **16.4 Procedures for recording and reporting Serious Adverse Events**

977 All serious adverse events will be recorded in the medical records and the CRF, and the  
978 sponsor's AE log

979 All SAEs (except those specified in section 16.5 as not requiring reporting to the Sponsor)  
980 must be recorded on a serious adverse event (SAE) form. The CI/PI or designated individual  
981 will complete an SAE form and the form will be preferably emailed to the Sponsor within 5  
982 working days of becoming aware of the event. The Chief or Principal Investigator will  
983 respond to any SAE queries raised by the sponsor as soon as possible.

984 Where the event is unexpected and thought to be related to the procedure this must be  
985 reported by the Investigator to the Health Research Authority within 15 days.

986 | Completed forms for unexpected SAEs must be sent within 5 working days of becoming  
987 aware of the event to the Sponsor

988 **Email forms to**  
[[contact]](mailto:[contact])

989

990

991

992 **Flow Chart for SAE reporting**

993

[figure not shown]

Formatted: Numbering: Continuous

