### 5.4 SAFETY DATA

The number (and proportion) of participants experiencing AE/SAEs will be reported. No formal statistical testing will be undertaken of the safety data.

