## 6.5 DESCRIPTIVE STATISTICS

Descriptive statistics of the data will be presented. This will include randomisation figures, demographics, COVID19 data and outcome measure data along with completeness levels to assess missing data.

For all descriptive statistics continuous measures will be reported with mean values and standard deviations and categorical variables presented with counts and related percentages. If data are not normally distributed, then medians and interquartile ranges will be reported. Categorical variables will be reported with counts and related percentages. The following data will be presented:

- Participant demographics and sample characteristics
- Outcome measures at each timepoint (listed in section 5.2)
- Cognitive Assessments of cognitive function (listed in section 5.2)
- \*Intervention data summary; number of sessions attended.

*\*Presented in unblind report once all primary analysis listed in this SAP is complete.*

All data will be presented overall and split by allocation group.

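### The SAP's only adverse-event summary is a headcount with no severity grade and no event counts, so an excess of severe non-serious or repeated events in one arm can be masked

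*Combined protocol and SAP*

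**What the plan says.** Protocol 16.2 sets the grading: "Each adverse event will be assessed for severity, causality, seriousness and expectedness". Section 16.2.1 has three severity grades, the top one being "The adverse event results in alteration, discomfort or disability which is clearly damaging to health". Seriousness is a separate matter of outcome; one criterion in 16.1 is that the event "requires hospitalisation or prolongation of existing hospitalisation". An adverse event is defined broadly, as "Any untoward medical occurrence in a patient or study participant", whether or not the study procedure caused it. Section 16.3 covers recording: "All adverse events will be recorded in the CRF with clinical symptoms and accompanied with" a short description and dates.

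The SAP deals with safety in two sentences in section 5.4. The output is: "The number (and proportion) of participants experiencing AE/SAEs will be reported". The second sentence is: "No formal statistical testing will be undertaken of the safety data". The list of descriptive data in SAP 6.5 and the table of collected data in SAP Appendix 1 contain no adverse-event item. SAP 6.5 ends with a general rule, "All data will be presented overall and split by allocation group", but safety is not among the items listed there, and 5.4 does not say that its summary is by arm.

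**The concern.** The headcount uses each participant once. Anyone with a single mild event is already counted and cannot be counted again for a severe event or for a run of events after successive sessions. The definition of an adverse event is wide, participants already have symptoms when they enter, and follow-up lasts six months, so a sizeable share of both arms could have at least one event. The more common such background events are, the less the headcount can separate the arms.

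The intervention is ten one-hour sessions with tasks in between. If it provoked more moderate or severe events that did not meet a seriousness criterion, the planned summary could still look much the same in the two arms, although the protocol asks for the grade that would show the difference.

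**Working it through.** **Inputs.** From the documents: 59 participants per arm (SAP 4.1), 1:1 allocation (SAP 4.2), and a summary of participants rather than events (SAP 5.4). Assumed, because the documents give no adverse-event rates: a background risk p of any adverse event, equal in both arms, and an independent excess r = 15 percentage points of moderate or severe events in the rehabilitation arm.

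**The plan's own figure.** There is no safety figure to reproduce, only the arm size. A two-sided 5% t-test with an effect of 0.7 SD and 90% power needs 43.87, so 44 per arm and 88 in total. Then 88 / 0.75 = 117.3, so 118, or 59 per arm. Both stated totals reproduce.

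**Dilution.** The any-event risk is p in control and p + (1 − p) × r in rehabilitation. The visible difference is therefore (1 − p) × r. The 95% half-width is 1.96 × √[p0(1 − p0)/59 + p1(1 − p1)/59], where p0 and p1 are the two any-event risks.

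| p | Any event, control v rehabilitation | Visible difference (points) | Participants of 59 | 95% half-width (points) |
|---|---|---|---|---|
| 30% | 30.0% v 40.5% | 10.5 | 17.7 v 23.9 | 17.1 |
| 50% | 50.0% v 57.5% | 7.5 | 29.5 v 33.9 | 17.9 |
| 70% | 70.0% v 74.5% | 4.5 | 41.3 v 44.0 | 16.1 |
| 90% | 90.0% v 91.5% | 1.5 | 53.1 v 54.0 | 10.5 |

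**What a graded row would show.** Suppose 10% of each arm has a background moderate or severe event. The moderate-or-severe row is then 10% v 0.10 + 0.90 × 0.15 = 23.5%, or 5.9 v 13.9 participants of 59. The difference is 13.5 points with a half-width of 13.3, and it does not depend on how common mild events are.

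**Second parametrisation.** Let severe events occur in 5% v 20% of participants, and non-severe events in a proportion b of both arms. The any-event risk is 1 − (1 − b)(1 − s), where s is the severe proportion. At b = 30% this gives 33.5% v 44.0%, and at b = 90% it gives 90.5% v 92.0%. The differences are again 10.5 and 1.5 points, while a severe row would show about 3 v 12 participants.

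**Sensitivity to independence.** If the extra events fell only on people who already had an event, the headcount would show no difference. If they fell only on people with none, it would show the smaller of r and 1 − p: the full 15 points at p = 30%, 50% or 70%, and 10 points at 90%. Repeat events in the same person are lost at every value of p.

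**The case against.** Five points can be made for the plan.

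- **Secondary outcomes.** Post-exertional malaise (DSQ-PEM), fatigue (Chalder), anxiety (GAD-7), depression (PHQ-8) and sleep (PSQI) are compared between arms at 3 and 6 months, adjusted for baseline, with 95% intervals (SAP 6.7 and Appendix 1). A reader might infer that the headcount is the trial's only safety comparison; it is not. Lasting worsening on these scales would be visible there. They do not cover transient flares or other kinds of event, and DSQ-PEM is analysed as present or absent, so worsening in someone already positive does not register. Nor is post-exertional malaise an entry criterion, so participants cannot be described as a population defined by it.
- **The grades are used elsewhere.** Protocol 16.4 uses causality and expectedness for reporting to the Health Research Authority, and 16.5 uses unusual frequency or severity to bring exempt serious events back into reporting. The protocol and SAP therefore do not contradict each other. The gap is that the SAP's summary leaves the grades out.
- **Separate rows.** The SAP's wording may already mean AE and SAE counts shown separately. Serious events would then be visible. Severe is not serious in this protocol, so severe non-serious events and all moderate non-serious ones would still be merged with mild ones.
- **Unknown rates.** No prompted adverse-event questioning is described, so recorded rates could be low. At p = 30% most of the excess still shows.
- **Unequal ascertainment.** The rehabilitation arm has ten extra contacts and participants know their allocation (protocol 7.3), so events may be noticed more fully in that arm. This stands, and it limits how any between-arm difference can be read.

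**Conclusion.** The point holds as a gap in the planned reporting of harms. The SAP summarises adverse events only as participants affected, without severity or event counts, and 5.4 leaves the split by arm unstated. An excess of moderate or severe non-serious events, or of repeated events, can therefore be masked. Under independence, an assumed 15-point excess shows as between 10.5 points (p = 30%) and 1.5 points (p = 90%).

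A reader might go further and conclude that a rise in severe events is hidden. The documents do not support that: the amount of masking depends on a background rate that they do not give, and at a low rate much of the signal would remain. The primary result, the sample size and the planned tests are unaffected.

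**What to change.** Amend SAP 5.4 to a descriptive table by arm, with AEs and SAEs in separate rows. For each, give the number of participants by maximum severity and the number of events by severity. Show relatedness descriptively only: it is a judgement, and controls have no sessions to which an event could be related.

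First confirm that the severity grade is held in the CRF or the AE log. Protocol 16.3 names symptoms, a description and dates but not the grade; 16.2.1 offers the categories as a guide; and 16.2.2 still contains template wording.

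If a risk difference with a 95% interval is given for moderate-or-severe events, attach a caveat that the ten extra contacts and open allocation may lead to fuller ascertainment in the rehabilitation arm. The statement against formal testing can stay.

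The cost is SAP wording and one more table, provided the grade is stored. SAP 6.1 expected data lock in August 2024 and analysis in September 2024; if analysis has already begun, label the table as added.

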### 952 16.2.1 Severity

953 The generic categories below are given for use as a guide.

| Category | Definition                                                                                                                                                               |
|----------|--------------------------------------------------------------------------------------------------------------------------------------------------------------------------|
| Mild     | The adverse event does not interfere with the participant's daily routine, and does not require further procedure; it causes slight discomfort                           |
| Moderate | The adverse event interferes with some aspects of the participant's routine, or requires further procedure, but is not damaging to health; it causes moderate discomfort |
| Severe   | The adverse event results in alteration, discomfort or disability which is clearly damaging to health                                                                    |

954

### 955 16.2.2 Causality

956 The assessment of relationship of adverse events to the procedure is a clinical decision  
957 based on all available information at the time of the completion of the case report form.

958 If a differentiated causality assessment which includes other factors in the study is deemed  
959 appropriate, please add/amend the following wording to specify:

960 It is of particular importance in this study to capture events related to the product application  
961 procedure. The assessment of relationship of an adverse event to this/these additional  
962 safety issue(s) will also be carried out as part of the study.

963 The differentiated causality assessments will be captured in the study specific CRF/AE Log  
964 and/or SAE form (amend as required).

965 The following categories will be used to define the causality of the adverse event:

| Category       | Definition                                                                                                                                                                                                                                                                                               |
|----------------|----------------------------------------------------------------------------------------------------------------------------------------------------------------------------------------------------------------------------------------------------------------------------------------------------------|
| Definitely:    | There is clear evidence to suggest a causal relationship, and other possible contributing factors can be ruled out.                                                                                                                                                                                      |
| Probably:      | There is evidence to suggest a causal relationship, and the influence of other factors is unlikely                                                                                                                                                                                                       |
| Possibly       | There is some evidence to suggest a causal relationship (e.g. the event occurred within a reasonable time after administration of the study procedure). However, the influence of other factors may have contributed to the event (e.g. the participant's clinical condition, other concomitant events). |
| Unlikely       | There is little evidence to suggest there is a causal relationship (e.g. the event did not occur within a reasonable time after administration of the study procedure). There is another reasonable explanation for the event (e.g. the participant's clinical condition).                               |
| Not related    | There is no evidence of any causal relationship.                                                                                                                                                                                                                                                         |
| Not Assessable | Unable to assess on information available.                                                                                                                                                                                                                                                               |

### 967 16.2.3 Expectedness

| Category          | Definition                                                                                                                  |
|-------------------|-----------------------------------------------------------------------------------------------------------------------------|
| Expected   | An adverse event which is consistent with the information about the procedure clearly defined in this protocol .     |
| Unexpected | An adverse event which is not consistent with the information about the procedure clearly defined in this protocol . |

968 \* this includes listed events that are more frequently reported or more severe than previously  
969 reported

970 **16.3 Recording adverse events**

971

972 All adverse events will be recorded in the CRF with clinical symptoms and accompanied with

973 a simple, brief description of the event, including dates as appropriate.

975

976 **16.4 Procedures for recording and reporting Serious Adverse Events**

977 All serious adverse events will be recorded in the medical records and the CRF, and the  
978 sponsor's AE log

979 All SAEs (except those specified in section 16.5 as not requiring reporting to the Sponsor)  
980 must be recorded on a serious adverse event (SAE) form. The CI/PI or designated individual  
981 will complete an SAE form and the form will be preferably emailed to the Sponsor within 5  
982 working days of becoming aware of the event. The Chief or Principal Investigator will  
983 respond to any SAE queries raised by the sponsor as soon as possible.

984 Where the event is unexpected and thought to be related to the procedure this must be  
985 reported by the Investigator to the Health Research Authority within 15 days.

986 | Completed forms for unexpected SAEs must be sent within 5 working days of becoming  
987 aware of the event to the Sponsor

988 **Email forms to**  
[[contact]](mailto:[contact])

989

990

991

992 **Flow Chart for SAE reporting**

993

[figure not shown]

Formatted: Numbering: Continuous

